**3.3.4 Human-AI Interaction**

The human-AI interaction in handling input data involves:

1. The EDX technician and/or physician performing the studies according to standard protocols
2. A research coordinator verifying data completeness and transferring it to the AI system
3. The AI system generating a preliminary report
4. The physician reviewing the AI-generated report alongside the raw data

**3.3.5 AI System Output**

The output will be formatted as a structured text document with sections clearly delineated, similar to conventional EDX reports but with standardized terminology and organization.

**3.4 Outcomes**

**3.4.1 Primary Outcome**

The primary outcome is the quality of EDX reports as measured by the AI-Generated EMG Report Score (AIGERS). This composite score (range 0-1) evaluates report quality based on:

1. Finding Score (50%): Accuracy and completeness of reported EDX findings
2. Clinical Diagnosis Score (50%): Accuracy and appropriateness of the clinical interpretation

The AIGERS score will be independently assessed by three board-certified neurologists who are not involved in the report generation and are blinded to the study arm.

**3.4.2 Secondary Outcomes**

1. Word count and comprehensiveness of reports
2. Physician satisfaction with the AI tool (5-point Likert scale survey)
3. Number of recommendations included in reports
4. Technical performance metrics for the AI system (sensitivity, specificity for detecting abnormal studies)
5. Inter-rater reliability of reports assessed by kappa scores

**3.5 Participant Timeline**

The study will follow a simple timeline:

1. Screening and enrollment prior to scheduled EDX appointment
2. Randomization on the day of the EDX study
3. EDX testing performed according to standard clinical protocols
4. Report generation (either AI-assisted or physician-only)
5. Quality assessment and data collection
6. No follow-up visits required for the study (though patients may have clinical follow-up as determined by their treating physician)

**3.6 Sample Size**

A trial with a sample size of 200 participants (100 per treatment group) will be conducted to rapidly assess outcomes. Should the results prove favorable, there is potential for expanding the sample size and the trial itself.

**3.7 Recruitment**

Participants will be recruited from patients referred for routine EDX testing at the neuromuscular clinic. All eligible patients will be approached for participation during a four-week period (January 21 to February 21, 2025). Based on clinic volume, we anticipate being able to enroll the required 200 participants within this timeframe.

**4. Methods: Assignment of Interventions**

**4.1 Allocation**

**4.1.1 Sequence Generation**

Participants will be randomized using a computer-generated random number sequence with a 1:1 allocation ratio.

**4.1.2 Concealment Mechanism**

Allocation will be concealed using sequentially numbered, opaque, sealed envelopes that will be opened only after the participant has been enrolled and immediately before the EDX study begins.

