**2. Introduction**

**2.1 Background and Rationale**

**2.1.1 Intended Use of the AI Intervention**

The INSPIRE AI framework is intended to assist neurologists in interpreting electrodiagnostic (EDX) tests (including electromyography and nerve conduction studies) and generating diagnostic reports. The primary purpose is to reduce documentation burden, standardize reporting, and potentially improve diagnostic accuracy. The intended users are board-certified neurologists who regularly perform EDX tests in clinical practice.

Within the clinical pathway, EDX studies are conducted to evaluate patients with suspected neuromuscular disorders. Currently, physicians manually interpret the raw data and compose reports, a process that is time-consuming and subject to variation in quality and completeness. The INSPIRE system will generate a preliminary report based on the raw EDX data, which will then be reviewed, verified, and edited by a neurologist before finalization. This is expected to streamline workflow while maintaining or improving diagnostic accuracy.

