**3.3.2 Input Data Acquisition and Selection**

The input data for the AI intervention will consist of:

1. Patient demographic information (age, sex, clinical indication)
2. Medical history relevant to neuromuscular outpatient clinic
3. Complete nerve conduction study data (tables of measurements)
4. Needle EMG recordings (quantitative and qualitative descriptions)
5. Visual representations of waveforms

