**4.1.3 Implementation**

The allocation sequence will be generated by a biostatistician not involved in patient enrollment. Research coordinators will enroll participants, and the treating neurologists will assign participants to interventions based on the randomization envelope.

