**4.2 Blinding**

Due to the nature of the intervention, the neurologists generating the reports cannot be blinded to the study arm. However, the three neurologists assessing the quality of the reports (outcome assessors) will be blinded to the method of report generation. Reports from both arms will be reformatted to a standard template to prevent identification of the study arm based on formatting or style.

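### The arm is revealed before the EDX study instead of before report writing, so data acquisition and discard decisions may be made with the arm known

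*Protocol*

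**What the plan says.** Protocol 4.1.2 states that envelopes are "opened only after the participant has been enrolled and immediately before the EDX study begins". Protocol 4.1.3 adds that "the treating neurologists will assign participants to interventions based on the randomization envelope". The participant timeline in 3.5 agrees: step 2 is "Randomization on the day of the EDX study", step 3 is "EDX testing performed according to standard clinical protocols", and the report is generated in step 4.

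On who performs the test, 3.3.4 names "The EDX technician and/or physician performing the studies according to standard protocols". Section 2.1.1 describes the intended users of the AI as "board-certified neurologists who regularly perform EDX tests in clinical practice". The data passed to the AI include "Needle EMG recordings (quantitative and qualitative descriptions") under 3.3.2.

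On blinding, 4.2 says that "the neurologists generating the reports cannot be blinded to the study arm", giving the nature of the intervention as the reason, and blinds the three outcome assessors. It does not mention the person who performs the test.

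**The concern.** The intervention is a draft report that the AI writes from finished EDX data, so it begins only when testing is over. The arm is nevertheless known one step earlier. Parts of an EDX study depend on the examiner, notably how many muscles are sampled and how fully the needle findings are described. An examiner who knows that the record will be fed to an AI may sample or describe differently from one who knows that a physician will write the report unaided.

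AIGERS gives half its weight to the accuracy and completeness of reported findings and half to the diagnosis drawn from them (3.4.1). Both halves rest on what was acquired. If acquisition differs by arm, the AIGERS difference combines an effect of AI on reporting with an effect of knowing the arm on testing. Blinded assessors and a common report template (4.2) cannot remove a difference that is already in the underlying data. Analysing every randomized patient would not remove it either.

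**Working it through.** The protocol gives no figure on this point that could be reproduced. The check sets its sections side by side.

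1. **When the arm becomes known.** Sections 4.1.2 and 3.5 agree that it is before testing. The order is stated consistently and is not a slip in one section.
2. **Who knows it.** Under 4.1.3 the treating neurologist does. Under 3.3.4 the study is done by a technician, a physician or both. The protocol does not say that the treating neurologist always performs the test, that a technician is told the arm, or that a technician is kept unaware of it. The supported statement is that the examiner *may* know the arm.
3. **Whether the intervention needs it.** Section 2.4 defines the arms solely by how the report is generated. The reason for not blinding in 4.2 applies to report writers and does not extend to performing the test.
4. **What limits differences in acquisition.** Testing follows standard clinical protocols for everyone (3.1, 3.5). Section 3.2.3 requires complete sensory and motor conduction studies, all standard measurements and a minimum of three muscles. Section 3.2.4 excludes incomplete measurement sets and non-standard recording. These rules leave little room in the nerve conduction data.
5. **What stays discretionary.** Three muscles is a floor, and the qualitative needle EMG descriptions have no stated format. Under 3.3.3, when some measurements are missing but the study can still be interpreted, discarding the report is left to the examiner.
6. **Whether the pressures are equal.** In 3.3.4 a coordinator checks completeness before transfer to the AI. In 3.3.3 data below the quality threshold are removed from AI analysis and logged as a technical failure. Poor-quality data are documented in both arms, but no matching completeness check is described for physician-only reports.
7. **Which comparisons are exposed.** The primary comparison of AI-assisted with physician-only reports is exposed. So is AI-alone against physician-only (5.2.2), if the AI-alone reports are the intervention-arm drafts. AI-alone against AI-assisted uses the same acquired data and is not affected by this route.

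**Can the direction be fixed?** Assume, for illustration only, 15 scorable findings per report and a Finding Score equal to the proportion reported. The protocol gives neither the item count nor the reference standard. Consider one extra finding recorded by the examiner:

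- Scored against a fixed list of 15 that was not yet fully covered, and included in the report: the Finding Score rises by 1/15 = 0.067, and AIGERS by 0.5 × 0.067 = 0.033.
- Scored against the patient's own record, with all 15 previously reported and the extra item reported: 15/15 becomes 16/16, a change of 0.
- Same standard, extra item left out of the report: 15/15 becomes 15/16 = 0.9375. The Finding Score falls by 0.0625, and AIGERS by 0.031.

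The same change in acquisition can raise AIGERS, leave it unchanged or lower it, depending on a scoring rule that the protocol does not state.

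**The case against.** The strongest defence is pragmatic. Section 2.2 seeks the added value of AI in real-world practice, and section 2.3 lists workflow among the secondary objectives. In routine use the examiner would know that an AI will draft the report, so any change in how the test is documented could be counted as part of the AI-assisted pathway. This has some force, but the primary objective concerns interpretation and report quality, and 2.4 separates the arms at report generation only. The protocol nowhere presents a change in testing as part of the intervention.

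A second defence is that standard protocols and the input-data criteria already constrain acquisition. That stands in part: they narrow the route without closing it, because the number of muscles above the floor, the descriptions and the discard decision remain open.

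Stronger readings are tempting and are not supported:

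- A reader might infer that the neurologist always performs the test unblinded. Section 3.3.4 allows a technician.
- A reader might see a failure of allocation concealment. Enrolment precedes opening of the envelope, so selection at enrolment is not at issue.
- A reader might attach an inflated false-positive rate. That would need an AIGERS standard deviation, a scoring rule and a size of bias, and the protocol supplies none of them.
- A reader might conclude that the result could not be attributed to the AI at all. That is too absolute: the documents show that a difference could arise, not that one does.

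**Conclusion.** The point holds as an avoidable route to bias. The arm is revealed before EDX acquisition, no blinding of the examiner is described, and the discretionary parts of the data feed both the AI's input and the report that AIGERS scores. Discard decisions can also be made with the arm known. The order of steps applies to all 200 planned participants. How many are tested by someone who knows the arm is not stated, and neither the direction nor the size of any bias can be derived from the protocol.

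The timing is certain from the text. That acquisition would differ by arm is a plausible assumption about examiner behaviour. The change is worth making because the early reveal serves no stated purpose and is cheap to remove.

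**What to change.** In 4.1.2, have the envelope opened only when three things are done: EDX acquisition is complete, the measurements and needle EMG descriptions are saved, and the data-quality decisions under 3.3.3 that rest on the EDX data are made and recorded. Opening then comes immediately before report writing. In 3.5, place randomization after testing and before report generation. Section 4.1.3 can keep the treating neurologist as the person who acts on the envelope. Technical failures of the AI itself will still arise after the arm is known and should be recorded separately.

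The change adds no staff or patients, and the envelope is still opened on the day of the study. The one real cost is in the control arm: the recorded data must be completed before the report is started. That is a minor documentation step which may differ slightly from usual practice, and the protocol should acknowledge it because section 2.2 presents the control arm as current standard of care.

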**4.1.3 Implementation**

The allocation sequence will be generated by a biostatistician not involved in patient enrollment. Research coordinators will enroll participants, and the treating neurologists will assign participants to interventions based on the randomization envelope.

**4.2 Blinding**

Due to the nature of the intervention, the neurologists generating the reports cannot be blinded to the study arm. However, the three neurologists assessing the quality of the reports (outcome assessors) will be blinded to the method of report generation. Reports from both arms will be reformatted to a standard template to prevent identification of the study arm based on formatting or style.

**5. Methods: Data Collection, Management, and Analysis**

**5.1 Data Collection Methods**

**5.1.1 Data Collection Instruments**

1. EDX raw data: Collected using standard EDX equipment (Viking or Synergy systems)
2. AIGERS assessment forms: Standardized forms for blinded reviewers to score report quality
3. Physician satisfaction surveys: Electronic surveys using REDCap
4. Time tracking software: To measure report generation time
5. AI system logs: To capture technical performance metrics

**5.1.2 Data Management**

All data will be stored on secure, password-protected servers with encryption. Data entry will be performed by trained research coordinators with regular quality checks. The database will include validation rules to minimize entry errors.

**5.1.3 Data Security for AI Systems**

The following specific security measures will be implemented for the AI system:

1. All API calls to the Azure AI platform will use encrypted HTTPS connections
2. Authentication will use Azure Active Directory with multi-factor authentication
3. Access to the AI system will be restricted to authorized users with role-based permissions
4. All system interactions will be logged with user identification, timestamp, and action details
5. Patient data will be de-identified before processing by the AI system
6. Data at rest will be encrypted using AES-256 encryption
7. Regular security audits will be performed to identify vulnerabilities
8. All system components will comply with HIPAA and local data protection regulations

### 5.2 Statistical Methods

#### 5.2.1 Sample Size

The study will enroll 200 participants (100 per arm) during the one-month study period at the neuromuscular outpatient clinic at Rambam Healthcare Campus. While we acknowledge that this sample size may be insufficient to detect small differences between groups, it will provide initial insights into the performance differences between AI-assisted and physician-only approaches and inform future larger studies if results suggest potential benefits.

#### 5.2.2 Primary Outcome Analysis

The primary analysis will compare the AIGERS scores between the AI-assisted physician group and the physician-only group. We will first check for normality using the Shapiro-Wilk test. If data are not normally distributed, which is anticipated based on similar metrics, we will use the non-parametric Kruskal-Wallis test for the primary comparison. A two-sided p-value <0.05 will be considered statistically significant.

In addition to the main comparison between intervention and control groups, we will also evaluate the AI-alone performance by comparing the AI-generated reports (before physician modification) with both the AI-assisted physician and physician-only groups using the same statistical approach.

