**3.2.3 Input Data-Level Inclusion Criteria**

1. Complete nerve conduction study data including sensory and motor studies
2. Complete needle EMG examination of at least three muscles
3. High-quality recordings with minimal artifacts
4. All standard measurements recorded (amplitude, latency, conduction velocity)
5. Patient demographic data and clinical history available

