#### 5.2.6 Subgroup and Exploratory Analyses

1. **Diagnostic Category Subgroups**: Separate analyses for common diagnostic categories (radiculopathy, mononeuropathy, polyneuropathy) if sufficient numbers are available in each subgroup.
2. **Normal vs. Abnormal Studies**: Stratified analysis comparing AI performance on normal versus abnormal EDX studies.
3. **Physician Experience**: Exploratory analysis of whether physician experience level modifies the effect of AI assistance.
4. **Error Pattern Analysis**: Detailed categorization and analysis of error types made by AI versus physicians.

All secondary and exploratory analyses will be clearly identified as such in reporting, and appropriate corrections for multiple testing will be applied when interpreting results.

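### The primary AIGERS comparison is unadjusted; stratifying it by the pre-randomisation referral indication would be a cheap gain in precision

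*Protocol*

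**What the plan says.** Section 5.2.2 defines the primary analysis: "The primary analysis will compare the AIGERS scores between the AI-assisted physician group and the physician-only group". If AIGERS is not normally distributed, which the section anticipates, "we will use the non-parametric Kruskal-Wallis test for the primary comparison". The significance rule is "A two-sided p-value <0.05 will be considered statistically significant". No covariate or stratum is named. Section 5.2.4 adds only the possibility of transformation. Section 4.1.1 describes a computer-generated 1:1 sequence and mentions no stratification.

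On size, section 5.2.1 says "The study will enroll 200 participants (100 per arm) during the one-month study period" and concedes that "this sample size may be insufficient to detect small differences between groups".

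Four places bear on case mix:

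- Section 3.2.1 requires every participant to have been referred for EDX testing.
- Section 3.3.2 lists "Patient demographic information (age, sex, clinical indication" among the inputs to the AI system. Clinical indication is named nowhere else.
- Section 3.2.3 requires "Patient demographic data and clinical history available", which does not name the indication.
- Section 5.2.6 plans "Separate analyses for common diagnostic categories (radiculopathy, mononeuropathy, polyneuropathy", where numbers allow, and a stratified look at normal versus abnormal studies.

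**The concern.** AIGERS gives half its weight to the accuracy and completeness of findings and half to the clinical interpretation (section 3.4.1). It is plausible that such a score depends on how hard the case is, and referral indication is a natural marker of that before the test. If so, differences between types of case add to the variance against which the arms are compared, and neither the allocation nor the test removes them.

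Precision is at stake. The trial concedes that it may miss small differences, so a baseline variable that explains part of the outcome would be worth using. Adjustment would also account for a chance difference in case mix between the arms, which the planned test cannot do for the particular sample drawn.

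**Working it through.** **Inputs from the protocol.** 100 per arm and two-sided 0.05. The protocol gives no effect size, SD or power, so 200 cannot be reproduced as a sample-size calculation. The detectable difference is computed instead.

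**Assumed.** A true standardised difference of 0.3 or 0.4, and R² (the share of AIGERS variance explained by indication) between 0.05 and 0.30. The protocol has no figure for either.

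**Step 1, unadjusted detectable difference at 80% power.** (1.960 + 0.842) × √(2/100) = 0.396 SD. For a rank test on normal data, divide by √(3/π): 0.405 SD.

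**Step 2, effect of adjustment.** The residual SD becomes √(1 − R²). The detectable difference is 0.396 × √(1 − R²), and the equivalent unadjusted trial has 200/(1 − R²) patients. Power is Φ(d / (√(2/100) × √(1 − R²)) − 1.960).

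| R² | Detectable difference (SD) | Equivalent unadjusted N | Power at 0.3 SD | Power at 0.4 SD |
|---|---|---|---|---|
| 0 | 0.396 | 200 | 56.4% | 80.7% |
| 0.05 | 0.386 | 211 | 58.6% | 82.7% |
| 0.10 | 0.376 | 223 | 60.9% | 84.6% |
| 0.20 | 0.354 | 250 | 66.0% | 88.5% |
| 0.30 | 0.331 | 286 | 71.8% | 92.2% |

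At 0.4 SD the gain is 82.7 − 80.7 = 2.0 points for R² = 0.05, and 92.2 − 80.7 = 11.5 points for R² = 0.30.

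**Step 3, the rank tests themselves.** With two groups, Kruskal-Wallis gives the same p-value as the Mann-Whitney test without continuity correction (0.7231 for both in a check). It was compared with the van Elteren test in two simulations of 3,000 trials per scenario.

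- *Total SD held fixed, four equal strata, difference 0.40 SD.* For R² of 0 / 0.05 / 0.10 / 0.20 / 0.30, power was 79 / 80 / 78 / 78 / 78% unadjusted and 78 / 81 / 82 / 86 / 90% stratified.
- *Skewed 0–1 score, four unequal strata, within-stratum effect held fixed.* Unadjusted versus stratified power was 76.9% vs 75.9% when indication was not prognostic. It was 74.7% vs 75.9% at a rank R² of about 0.06, 73.0% vs 77.7% at about 0.13, and 62.7% vs 75.0% at about 0.27. Unadjusted power falls here because the stratum differences add to the total variance.

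In the second simulation, type I error lay between 4.3% and 5.6% for both tests. The simulation error of one power estimate is about √(0.8 × 0.2 / 3000) = 0.7 points, so gaps of about a point are approximate.

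**Step 4, chance imbalance.** For an indication with prevalence p, the standard error of the difference between arms is √(2p(1 − p)/100). The chance of a gap of 10 percentage points or more is 7.7% for p = 0.2, 12.3% for p = 0.3 and 14.9% for p = 0.4.

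**The case against.** The strongest reply is that an unadjusted comparison in a randomised trial is valid and common. Its variance already allows for chance imbalance, and the trial presents itself as giving initial insights. This stands: the simulated type I error shows no fault, and nothing here is a bias.

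A reader might infer more from the protocol than it says, in two ways.

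- *That indication is recorded for every patient in both arms before randomisation.* Section 3.3.2 lists it only as an AI input, and section 3.2.3 asks for demographic data and history. Referral under section 3.2.1, with the envelope opened immediately before the test (section 4.1.2), makes it very likely that an indication exists beforehand. That remains an inference.
- *That the protocol itself expects indication to matter.* Section 5.2.6 concerns diagnostic category and normal or abnormal result. Planning a subgroup analysis asks whether results differ; it does not state that referral indication predicts AIGERS.

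The benefit is also assumed. AIGERS rates a report against its own case, so its variance may come mainly from the reporting physician or from a ceiling, and a large residual category of indication would shrink any gain.

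An unseen SAP could add an adjusted analysis. That does not remove the point, because section 5.2.2 already names the primary test in the expected case and that test cannot take strata.

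**Conclusion.** The point holds as a missed gain in precision and should be labelled a cheap improvement. The documents do not support calling the planned analysis biased or wrong.

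The size depends wholly on how strongly indication predicts AIGERS. At 0.4 SD the formula gives about 2 points of power for an R² of 0.05, and the rank-test simulations give about 1 point (80 to 81%; 74.7 to 75.9%). At the upper end of the assumed range the gain is about 11 to 12 points (80.7 to 92.2%; 78 to 90%; 62.7 to 75.0%). If indication is uninformative, the loss is about 1 point. A small possible loss against a moderate possible gain favours stratifying, provided that the indication can be taken from the referral in both arms.

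**What to change.** In section 5.2.2:

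1. State that the indication category (suspected radiculopathy, mononeuropathy, polyneuropathy or other) is taken from the pre-randomisation referral in both arms. It is coded by someone blind to arm, before outcome data are seen, with a rule for multiple or non-specific indications.
2. Make the van Elteren stratified Wilcoxon test the primary rank test. If means are compared, use a linear model with arm and indication.
3. Report the unadjusted test as a sensitivity analysis.
4. Do not adjust the primary comparison for the EDX-derived diagnosis or the normal/abnormal result. Both arise after the envelope is opened.

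The cost is a change of wording, one four-level variable coded from the referral with a short coding rule, and about 1 point of power if indication proves uninformative. It needs no extra patients or visits. If the referral turns out not to state an indication consistently in both arms, the field must be collected at enrolment, before the envelope is opened.
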